In addition to the main analyses described above, we also anticipate adequate power for the planned mediation analysis. For the mediation analysis, simulation studies revealed that a sample size of 500 is adequate to detect pathways with small standardized effect sizes (as low as 0.14) at 80% power with methods described above [44].

#### Data collection

Data sources include the following: (1) standardized BP and anthropometric measurements at baseline and at 3, 6, and 12 months after trial enrollment; (2) quantitative participant surveys at baseline and at 3, 6, and 12 months after enrollment; (3) post-media interviews after each installment of the storytelling intervention for the intervention group; (5) medical record review; (6) implementation data gathered by the research coordinator and CHWs that will inform progress toward specific study milestones; and (7) semi-structured interviews for qualitative data.

##### Blood pressure and anthropometric measurement

As previously described, certified study nurses will be trained to measure BP according to a standardized protocol approved by the World Health Organization [45]. We used this protocol in our previous randomized trial of storytelling in Vietnam. This protocol was written for use with the *OmROn* HEM-8712 automated BP monitor, with special attention to assessment and maintenance of the instrument’s accuracy and training/certification of research assistants. Using a proper cuff size, measurements are taken after sitting quietly for 5 min, with the arm supported on a flat surface, with the upper arm at heart level. Three measurements are separated by at least 1 min, and values from the last two measurements will be averaged. Height and weight will be measured in the absence of shoes and heavy clothing while waist and hip sizes will be measured by placing the tape horizontally around the smallest part of the waist and the widest portion of the hips, respectively.

##### Participant surveys

All survey items will be taken from validated instruments, with scales or sub-scales left intact to preserve psychometric properties [46]. The survey will be implemented in a computer-assisted format and pilot tested for acceptability. The target duration time for the final survey will be less than 1 h. We will collect information on patient’s level of education, occupation, and economic circumstances using the WHO STEPs protocol [47, 48]. STEPs will also be used to collect data on CVD risk factors including tobacco use, alcohol consumption, salt intake, and physical activity. Adherence to anti-HTN medications will be measured using standardized forms previously developed by Duke University [49]. The Medication Adherence Self-efficacy Scale (MASES) instrument [50, 51] will measure self-efficacy in HTN management. Quality of life will be measured by the short form 12 questionnaire health survey (SF-12) [52]. All the survey measures previously existed in Vietnamese or have been translated and tested by our team as part of our previous work [15] with the exception of the adherence to anti-HTN medications, which will be translated following the set of best practices developed by the US Census Bureau [53]. Translation will be accomplished by a translation team led by study PIs, with multiple versions prepared in parallel followed by team meetings to reconcile possible differences. This approach has been shown to be superior to the simple “back-translation approach” in which translation by a single individual is translated back into the source language for review of accuracy [54]. Translation will include cognitive interviews with five participants drawn from the local community. Cognitive testing will identify constructs specific to the Vietnamese language and culture so that appropriate adjustments may be made to ensure cross-cultural equivalence [55]. Several cycles of revision will be accomplished at full translation committee meetings conducted in person and by Internet video link.

Post-DVD viewing interviews for intervention participants will be based on protocols previously developed by our team. The post-DVD viewing interviews using a structured questionnaire will collect self-reported engagement with the DVDs, including total viewing minutes, specific segments that were viewed, and whether the DVD was shared with family or friends. “Transportation” is a validated concept measuring absorption into the video story that has been linked to intervention effectiveness and is measured by a validated scale [56, 57]. Participants will be asked to elaborate on what motivated/hindered their intervention engagement.

#### Data management

Data will be stored on a Health Insurance Portability and Accountability Act (HIPAA)-compliant secure server with daily backup at the Health Strategy and Policy Institute and managed by the study data manager who is familiar with the REDCap database. This person will work closely with the PIs and experts at University of Massachusetts Medical School to make sure that the data are managed properly.

#### Study outcomes

##### Primary outcomes

Change in patient’s systolic BP levels over the 1-year follow-up period is the primary trial outcome. Registered nurses will be trained and certified to measure patient’s BP according to a protocol approved by the World Health Organization [45]. Three measurements of BP will be carried out, and values from the last two measurements will be averaged with the first reading ignored.

##### Secondary outcomes

Changes in diastolic BP, risk factors for CVD, medication adherence, self-efficacy, quality of life, cost, and implementation outcomes are secondary outcomes of this study. The WHO STEPs survey, which has been used to investigate the epidemiology of HTN in the Vietnamese language [48], will be used to collect data on several risk factors for CVD. Costs include the following: (1) program costs, which consist of costs to develop the intervention and implementation costs incurred at the district and community levels, and (2) patient costs such as drugs, diagnostic procedures, time lost, health center visits, and consultation fees.

Implementation outcomes including acceptability, appropriateness, adaptation, feasibility, fidelity, and sustainability will be collected via semi-structured interviews and focus group discussions among stakeholders and patient interviews, and post-DVD viewing surveys at follow-up visits. The implementation data and barriers to study milestones achievement gathered by the research team will inform strategies to overcome barriers and progress toward specific study milestones.

#### Data analysis plan

##### Qualitative analysis

In particular, we will use a well-accepted type of qualitative analyses often described as thematic analysis. Thematic analysis will be applied to the narratives obtained via Story Development Groups as well as from individual interviews from Video Stars and will proceed as follows: (1) entering transcripts into NVivo (qualitative software), (2) performing initial in vivo coding to separate the full story into initial story units, (3) tagging story units with codes from pre-existing codebook as well as any additional themes that emerge, and (4) grouping related codes based on broader themes connecting the experiences of participants to key concepts from our conceptual frameworks, which will be explored in the intervention. Thus, our approach to thematic analysis will include open coding, followed by concept building, and the development of themes/categories [58, 59]. Three members of the team will code these data—using the Link and Phelan framework [60] as a guide. Rich data will be gathered from multiple sources to drive the qualitative analyses. Interview notes and recordings from the Story Development Groups and interviews of Video Stars will be linked by a code, and recordings will be destroyed after verification of notes.

For needs assessment study, we will also utilize thematic qualitative analysis utilizing the qualitative software platform NVivo to objectively identify and catalog the perceptions expressed in these interviews. The interviews will be analyzed utilizing a thematic analysis approach to identify central themes as they appear in interviews. The identified overarching themes will serve as a baseline to build upon the packaged narratives to be presented visually in the DVDs.

Detailed field notes and codebooks will be maintained. Qualitative data analysis software will support the coding activities for the thematic analysis process above and will allow for inter-rater reliability testing among multiple coders, who will achieve at least a 90% agreement rate.

##### Quantitative analysis

We will begin the statistical analysis by examining univariate statistics, including measures of central tendency and dispersion. We will carefully document the trial recruitment and retention process with a CONSORT diagram [61, 62]. In accordance with best practice, differences in baseline characteristics of the intervention and comparison groups will be established based on standardized differences, rather than on tests of statistical significance [63, 64].

All primary hypothesis testing will be performed on an intent-to-treat basis and will be two-sided with alpha error will be set at 0.05. For the main study hypothesis, the continuous outcomes will be systolic (H1) and diastolic (H2) BP. We will use a generalized linear mixed model adjusting for important potential covariate imbalances between the two primary study comparison groups. Since we will collect longitudinal data with repeated observations nested within participant, and participants nested within community, many statistical analyses will be based on a generalized linear mixed model with Restricted Maximum Likelihood (REML) estimation that accounts for the complex data structure through random effects response [65–68].

We will use mediation analysis to disentangle the multiple mechanisms which may be associated with the effectiveness of our multi-level intervention. Patient-level mediators of intervention effectiveness include the following: (1) intervention engagement (measured by number of CHW sessions completed and time spent in the sessions, types of goals set and corresponding action plans, BP self-monitoring, and engagement with the storytelling intervention), (2) medication adherence, (3) adherence to heart-healthy lifestyle recommendations, and (4) patient activation. Clinic-level mediators include implementation of standardized BP measurement protocols, engagement of physicians and nurses in the trial educational programs, and fidelity of CHW intervention delivery.

For the secondary analysis, we will examine differential over-time changes in diastolic BP, HTN control, and CVD risk, using statistical approaches described above for testing the main study hypothesis. For these analyses, a dichotomous measure of BP control will be constructed according to JNC-8 [38]. Overall risk of a CVD event at 10 years will be calculated based on the Asian Pacific Cohort equation [69]. We will examine changes in patient’s individual risk factors for CVD (e.g., smoking, physical inactivity) as well. We will carry out exploratory analyses for possible heterogeneity of intervention effect among sub-groups of participants defined by age, sex, and existing CVD.

Missing data may introduce potential bias, and the most important defense to minimize missing data on key factors is advanced planning [70, 71]. In our previous work, we have developed successful plans to maximize participant retention and obtain complete data through sound principles of data collection and quality control [15]. Sensitivity analyses will estimate the bounds of potential bias introduced by omissions. Under the missing-at-random assumption, multiple imputation [72] will generate plausible values of missing covariates while accounting for the additional uncertainty introduced by the omissions. All the analyses will be performed using STATA 16.0 (Stata Corp, TX).

The economic analysis will be led by [name], who has expertise in evaluating the cost-effectiveness of interventions to prevent CVD in Vietnam [73]. From the societal perspective, we will analyze costs and effectiveness for the intervention package with the proposed enhancements in comparison to standard implementation of the Vietnam National HTN Program, using approaches appropriate for lower-to-middle income countries [74, 75]. Costs include the following: (1) program costs, which consist of costs to develop the intervention and implementation costs incurred at the district and community levels, and (2) patient costs such as medications, time lost, health center visits, and consultation fees. We will calculate the incremental costs of the intervention by subtracting the average costs for the intervention group from the average costs for the comparison group. The incremental cost-effectiveness ratio will be calculated as the additional cost of the intervention divided by the change in both systolic and diastolic BP related to the intervention. In addition, we will calculate cost-effectiveness ratios for BP control, by dividing the additional costs of the intervention by the proportion who achieved HTN control as a result of the intervention. Because this is a country-specific economic analysis, all costs will be evaluated using the Vietnamese Dong (VND) with subsequent conversion to US dollars. We will perform one-way sensitivity analyses related to variable intervention effectiveness, variable engagement, and trial adherence.

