#### Study sites

A total of 16 eligible communes in 4 districts in Hung Yen province will be randomly assigned to either the intervention (*n* = 8) or the comparison group (*n* = 8). Each of the selected communes satisfies the following criteria: (1) have a CHC with a medical doctor, (2) are not currently participating in other studies for HTN control, and (3) have a minimum geographic separation of 12 km (7 miles) from all other study communities to minimize possible contamination. Eligible and consenting trial participants with uncontrolled HTN (*n* = 680; approximately 43 patients per commune) will be assigned to intervention versus comparison status based on the community in which they reside.

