#### Participant eligibility

To be enrolled in our pilot study, consenting adult men and women must fulfill each of the following criteria: (1) be a resident of the selected commune and have no plans for moving during the next 12 months after trial enrollment; (2) be aged 25 years or older, a cutoff which is commonly used in population-based surveillance studies of HTN in Vietnam [6, 8]; (3) have a diagnosis of uncontrolled HTN according to the 8th Joint National Commission of High Blood Pressure (JNC 8) [38]; (4) not be cognitively impaired (as assessed by study physicians); (5) not be a “story teller” used to develop the intervention; (6) not be a family member of another participant in the study; and (7) not pregnant.

In addition, those diagnosed with elevated BP for the first time will be invited for re-measurement of their BP over the next 2 weeks (minimum of 1 week apart) after their initial CHC visit. If their average BP remains elevated, these persons will be invited to participate in the trial. Trained study nurses at study sites will obtain informed consent from eligible patients. Both newly diagnosed and prevalent patients with HTN (treated or otherwise) will be enrolled. If they are not treated at the time of trial enrollment, they will be referred to their district health centers for a follow-up exam and initiation of treatment, which will be covered by public health insurance. Members of the study team will work closely with doctors at the district health centers to follow up these patients.

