#### Study recruitment and randomization

Sixteen communities will be randomly assigned to either the intervention or the comparison condition stratified by districts using the STATA program. In each district, 2 communes will be randomly assigned to the intervention group and 2 communes will be randomly assigned to the comparison group. Patients will be recruited from the community setting. Screening events to identify patients satisfying our study criteria will be conducted at local CHCs. A second screening visit will be scheduled for eligible patients with elevated blood pressure (BP) values (systolic BP ≥ 140 mmHg, or diastolic BP ≥ 90 mmHg) 2 weeks later, at which time their BP will be re-measured and written informed consent will be obtained. Individuals who are found to have elevated BP at the time of clinic screening and are not willing to participate in the study will be referred for usual care at local district health centers.

The recruitment will rely on CHWs embedded in both the clinic and the community, which will provide credibility and trust. The CHWs and study nurses will offer BP screenings at their CHCs. With this approach, our recruitment goals will achieve in the allotted time.

After enrollment, a reminder letter will be sent to all participants before each of the follow-up visits. One week before the scheduled follow-up visit, local staff will contact study participants by phone. Because the communes are small, it is easy to visit participant’s homes. If patients miss their follow-up visit, local staff will contact them by phone to remind them to come into the CHC or visit their homes to measure their BP, if necessary. Patients can withdraw from the study at any time during the study period. If patients move out from their communes permanently, they will be considered as dropping out from the study.

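### BP control is zero or nearly zero at baseline by eligibility, so its planned analysis as differential change over time does not suit it; compare the proportion controlled at 12 months instead

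*Protocol article*

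**What the plan says.** Under Participant eligibility, patients must "have a diagnosis of uncontrolled HTN according to the 8th Joint National Commission of High Blood Pressure (JNC 8"). Study sites describes the 680 to be enrolled in the same terms: "Eligible and consenting trial participants with uncontrolled HTN". Study recruitment and randomization sets a second screening visit for people with raised readings ("systolic BP ≥ 140 mmHg, or diastolic BP ≥ 90 mmHg) 2 weeks later, at which time their BP will be re-measured"). For people diagnosed for the first time, Participant eligibility adds: "If their average BP remains elevated, these persons will be invited to participate in the trial".

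The last part of Quantitative analysis says that "a dichotomous measure of BP control will be constructed according to JNC-8". It lists control with diastolic BP and CVD risk, to be examined as "differential over-time changes in diastolic BP, HTN control, and CVD risk, using statistical approaches described above" for the main hypothesis. Those approaches were laid out for systolic and diastolic BP as continuous outcomes, with repeated observations nested in participants and participants nested in communes. Many of the analyses are to use a "generalized linear mixed model with Restricted Maximum Likelihood (REML) estimation". BP is measured at baseline and at 3, 6 and 12 months (Data collection).

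The economic analysis uses a different quantity for the same outcome. It divides the additional cost by the share of patients who reached control because of the intervention.

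**The concern.** Change from baseline is a natural target for systolic BP, which varies between patients at entry. It is a poor target for a yes/no outcome that the entry criteria have already fixed at no. Eligibility and outcome cite the same standard, so the baseline rows carry almost no information about control, yet the stated target is a difference between arms in change from those rows.

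Control is likely to be the result that policymakers read first. If the analysis follows the text in the usual way (logit link, baseline as one of the repeated outcomes, group-by-time term), the analyst will get either a fit that does not settle or an estimate governed by a few baseline readings. The model would then have to be replaced after the data are in view, which a pre-specified plan is meant to avoid.

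**Working it through.** The article states no expected control rate and no sample size for control, so there is no figure of the plan's own to reproduce.

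**Inputs.** From the article: 680 patients, 1:1 by commune, so 680/2 = 340 per arm; 16 communes, 8 per arm, in 4 districts. Assumed for illustration: 12-month control of 35% (comparison) v 45% (intervention), no losses, no clustering and no random effects. The counts are 0.35 × 340 = 119 and 0.45 × 340 = 153.

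**Step 1: follow-up contrast only.**
- Log odds ratio = ln(153/187) − ln(119/221) = −0.201 + 0.619 = 0.418.
- SE = √(1/153 + 1/187 + 1/119 + 1/221) = √0.0248 = 0.158.
- Risk difference = 0.45 − 0.35 = 0.10.

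**Step 2: logit change from baseline, nobody controlled at baseline (0/340 v 0/340).** The contrast is the follow-up log odds ratio minus the baseline log odds ratio. The latter needs ln(0/340) in each arm, which is undefined. Fitting group, time and group × time by iteration shows this:

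| Iterations | Baseline log-odds | SE of group × time |
|---|---|---|
| 10 | −11.6 | 15 |
| 25 | −26.6 | 27,313 |
| 50 | −37.7 | 5.1 million |

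The printed interaction stays at 0.418 only because both baseline cells drift together. With 0 controlled in the comparison arm and 3 in the intervention arm, the interaction itself drifts: −6.4, −21.4, −33.8. Random effects for participant and commune would not supply the missing baseline events.

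**Step 3: a few patients controlled at baseline (assumed 5 comparison, 3 intervention, of 340 each).**
- Baseline log odds ratio = ln(3/337) − ln(5/335) = −4.721 + 4.205 = −0.517.
- Interaction = 0.418 + 0.517 = 0.935.
- Variance = (1/3 + 1/337 + 1/5 + 1/335) + 0.0248 = 0.5393 + 0.0248 = 0.5641; SE = 0.751.
- The baseline cells supply 0.5393/0.5641 = 96% of the variance. The SE is 0.751/0.158 = 4.8 times that of Step 1.
- With the two baseline counts swapped (3 comparison, 5 intervention), the interaction is 0.418 − 0.517 = −0.099. Moving two readings each way reverses the sign while the 12-month data stay the same.

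**Step 4: risk-difference scale.** With 0 v 0 at baseline, the difference in change is (0.45 − 0) − (0.35 − 0) = 0.10, identical to the 12-month difference. With 5 v 3 it is (153 − 3)/340 − (119 − 5)/340 = 150/340 − 114/340 = 0.106. On this scale the problem almost disappears.

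**The case against.** The strongest reply is that the failing model is not written down. The article names a generalized linear mixed model, which can handle binary outcomes, but gives no link, no odds ratio and no statement that baseline is a row of the outcome. Such details are commonly left to an SAP. That stands in part: the absence of a link function is not the point here. What the article does state is the target (differential change over time) and the method (that of the continuous main hypothesis), and together they fit this outcome badly.

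Three stronger readings are tempting, and the document does not support them.
- *The analysis of control cannot be estimated at all, because every patient is uncontrolled at baseline.* Only the odds-ratio change from baseline fails. Contrasts at 3, 6 or 12 months, changes between follow-up visits, and risk differences can all be estimated. Nor is exactly zero guaranteed: the requirement that BP remain raised is stated for first diagnoses, and the recruitment section does not say that the repeat reading must be raised in known patients.
- *REML rules out a binary outcome, or the standard error will be too small.* The article assigns REML to many analyses, not all, and REML-type methods for generalized linear mixed models exist. A standard error that is too small was not shown; in the check above it explodes.
- *The cost-effectiveness ratio for control is compromised.* That ratio already uses the proportion reaching control, a follow-up quantity.

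**Conclusion.** The point holds in limited form. By design, control at baseline is zero or nearly zero in both arms. Differential change from baseline in control, analysed on the logit scale with the approach set for continuous BP, is then inestimable (0 v 0 of 340) or too unstable to use (0.94, SE 0.75, at 5 v 3 of 340, against 0.42, SE 0.16, from the 12-month data alone).

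The sizes rest on assumed control of 35% v 45%, assumed baseline counts, and fits without clustering. The failure at 0 v 0 does not depend on the follow-up rates. The conclusion also relies on eligibility and outcome sharing the JNC 8 label, since the article does not spell out cut-points for the control outcome.

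The reach is one secondary outcome. The primary systolic BP analysis, the sample size and the economic ratio for control stand as they are. The change should be made, but it does not threaten the trial's main conclusion.

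**What to change.** In the secondary-analysis part of Quantitative analysis, separate control from diastolic BP and CVD risk, and state:
- The outcome is the proportion controlled by the JNC 8 definition at 12 months, with 3 and 6 months supportive.
- Baseline control status is not part of the outcome data. Baseline BP enters as a covariate.
- Arms are compared with a binary model or a commune-level analysis of proportions, adjusted for baseline BP and district, with commune as the cluster and a small-sample correction for 16 communes. A commune-level analysis has 16 − 2 = 14 degrees of freedom, or 14 − 3 = 11 after three district terms.
- The result is reported as a risk difference, so that it matches the proportion used in the economic analysis.

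Adding hypertension control to the list under Secondary outcomes would be tidy, but is not essential. The cost is analysis wording only; visits, measurements and sample size do not change.

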**Discussion:**

Results from this full-scale trial will provide health policymakers with practical evidence on how to combat a key risk factor for CVD using a feasible, sustainable, and cost-effective intervention that could be used as a national program for controlling HTN in Vietnam.

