### Study setting

The study will be conducted in the Red River Delta Region in northern Vietnam. In this region, communes (communities) in Hung Yen province were selected based on their general representativeness. Hung Yen province has a population of approximately 1.3 million, organized into 10 districts and 161 communes. In Vietnam, the health system is organized into four levels, namely central, provincial, district hospital, and the lowest level, which includes the community health centers (CHCs) that are responsible for providing primary health care and outpatient services. Patients with HTN are typically treated and managed at the district health centers unless they need to be referred for a higher level of care.

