#### Timeline

The proposed study will take place over a 5-year period. During the first 6 months of year 1, we will conduct a needs assessment study. The next 18 months will be devoted for intervention enhancement development. Training for intervention delivery will be conducted in early year 3, right before the trial start (year 3). All data collection activities for the trial will be completed by mid-year 5. Year 5 will be devoted to data analysis and manuscript writing.

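### Both cost-effectiveness ratios include one-off development cost averaged over about 340 trial patients, and no planned sensitivity analysis varies that cost or the scale of use

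*Protocol article*

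**What the plan says.** The economic paragraph under Quantitative analysis (Protocol article) takes a societal perspective and lists two kinds of cost. The first is "program costs, which consist of costs to develop the intervention and implementation costs incurred at the district and community levels". The second is patient costs. Secondary outcomes repeats the first definition: "costs to develop the intervention and implementation costs incurred at the district and community levels".

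The incremental cost is the difference between the two groups' averages, obtained by "subtracting the average costs for the intervention group from the average costs for the comparison group". The main ratio is the "additional cost of the intervention divided by the change in both systolic and diastolic BP related to the intervention". A second ratio divides the same additional cost by the proportion brought under control because of the intervention. The listed uncertainty work is "one-way sensitivity analyses related to variable intervention effectiveness, variable engagement, and trial adherence".

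Development is a separate phase that ends before the trial starts. Timeline says: "The next 18 months will be devoted for intervention enhancement development". The discussion part of the Abstract gives the purpose as evidence on a "cost-effective intervention that could be used as a national program", and the Dissemination plan describes scale-up with the Ministry of Health.

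**The concern.** Development (new patient stories, four storytelling DVDs) is largely paid once, however many patients later use the materials. An average over trial patients turns this fixed sum into a per-patient cost whose size depends on how many patients were enrolled. That number was set by the power calculation and says nothing about how widely the programme would be used.

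A policymaker deciding on adoption needs the cost of delivering the enhancements at the scale considered, with development shared over all users. A single all-in ratio from the trial answers a different question: what it cost to create the package and run it for this arm. Since none of the planned sensitivity analyses moves development cost or scale, a reader could not get from one answer to the other. The tendency is to make the enhancements look dearer than they would be in wider use.

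**Working it through.** The article states no cost and no ratio, so there is no plan figure to reproduce. The check is algebraic, and every cost input is an assumption.

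**Inputs from the document**
- Patients: 680 in 16 communes, 8 per arm (Study sites). 680/16 = 42.5 per commune, matching the stated figure of approximately 43. Intervention arm: 8 × 42.5 = 340.
- Planned difference in systolic change: 5 mmHg (Sample size).
- Province: "organized into 10 districts and 161 communes" (Study setting).

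**Notation**
- D = development cost of the intervention arm beyond that of the comparison arm.
- c = all other incremental cost per patient.
- n = patients in the intervention arm.

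The increment is taken as intervention minus comparison. The printed sentence has the subtraction the other way round; that is a separate matter and affects only the sign.

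**Dependence on trial size**

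Incremental cost per patient = c + D/n. Ratio per mmHg = (c + D/n)/5, so the development term is D/(5n).

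| n | Development term per mmHg |
|---|---|
| 170 | D/850 |
| 340 (planned) | D/1,700 |
| 680 | D/3,400 |

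Doubling the arm halves the term, with the programme and its effect unchanged.

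**Illustrative size against province-wide use**

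Assume the same 42.5 patients per commune: 161 × 42.5 = 6,843 patients, and 6,843/340 = 20.1. Write D = k × 340c, so k is development cost relative to all other incremental cost in the arm. The trial ratio is then (1 + k) times the ratio without development cost, and the province-scale ratio is (1 + k/20.1) times it.

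| k (assumed) | Trial | Province | Trial ÷ province |
|---|---|---|---|
| 0.1 | 1.10 | 1.005 | 1.09 |
| 0.5 | 1.50 | 1.025 | 1.46 |
| 1 | 2.00 | 1.050 | 1.91 |
| 2 | 3.00 | 1.099 | 2.73 |

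**If development partly recurs**

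Suppose a fraction r of D must be spent again for each further 340 users. With k = 1 and r = 0.5, the province multiplier is 1 + (1 + 0.5 × 19.1)/20.1 = 1.52, and 2.00/1.52 = 1.31. The overstatement shrinks from 91% to about 31%. It vanishes only at r = 1, when development is repeated in full.

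**Planned sensitivity analyses**

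Effectiveness, engagement and adherence are varied. None of them is a change in D or in the number of users over whom D is shared.

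**The case against.** Four objections have weight.

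- **Perspective.** Resources spent on development are real costs to society, and the stated comparison is of the package as tried with standard implementation. Including them is a legitimate choice. This stands. A reader might infer that development cost should be taken out of the planned ratio, but the document does not support that.
- **Allocation rule.** The article never says that all of D is divided by trial patients. It refers to costing methods for lower-to-middle income countries that are not at hand, and a fuller plan may annuitise. This stands as a caution, and it is why the point rests on the plain reading of average group costs. Annuitising would shrink D but leave its dependence on n. Only apportioning D to a target population would remove that, and nothing stated does so.
- **Not purely one-off or incremental.** Storytelling materials existed from the pilot, yet the Storytelling section plans new stories for a wider community base, so expansion may bring further development. Comparison patients also receive newly made Learn-More DVDs, and the needs assessment serves both groups, so part of the cost cancels. This stands. It rules out the stronger inference that adoption would incur no development cost, and a ratio with no development cost could understate the cost of roll-out.
- **Scale is not peculiar to development.** Training of community health workers is also largely fixed or stepped by site. This is true, and it supports an analysis by scale.

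None of these makes a single all-in ratio sufficient for a decision about wider use.

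**Conclusion.** The point holds as a cheap improvement to the stated analysis; it does not show that the planned ratio is invalid. On the plain reading, the incremental development cost enters both ratios divided by about 340, so part of each ratio depends on trial size. The ratio then tends to overstate the cost per patient of wider use. The direction needs only that incremental development cost is positive and not fully repeated at roll-out.

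The size cannot be computed from the document. The 9% to 173% range rests on assumed values of k, on the trial's recruitment number per commune standing in for the number treated, and on no recurring adaptation. It should not be read as an estimate. Nor does the document show that the enhancements would be judged not cost-effective for this reason. Cost is one of several secondary outcomes, and the primary blood pressure inference is untouched.

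**What to change.** In the economic paragraph under Quantitative analysis:

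1. Report each ratio (per mmHg and for control) both with and without development cost.
2. Print total development cost separately, with the part attributed to each arm.
3. Add a one-way sensitivity analysis that spreads development cost over stated populations (trial, province, national), with an explicit allowance for recurring adaptation of stories and materials.

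The planned all-in ratio can stay. The plan already names development and implementation as separate components, so the design does not change. The cost is a few sentences, extra rows in the results, and two versions of each ratio to interpret instead of one.
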